#### Shedding criteria.

Subjects who, despite providing informed consent form and passing the screening process to obtain a randomization number, are unable to complete the treatment regimen and observation period specified in the study protocol are considered shedding cases.

#### Management of shedding cases.

When a subject is shed, efforts should be made to contact them via home visits, scheduled follow-ups, telephone calls, or letters to determine the reasons for shedding. Relevant information should be recorded, including the date of the last acupuncture session and the evaluation items completed up to that point. All data pertaining to shedding cases should be carefully preserved, both for archival purposes and for inclusion in intention-to-treat (ITT) statistical analysis.

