#### Termination criteria.

(1)At least one urologist or gynecologist must participate in this study. If a patient experiences severe adverse reactions that, in the physician’s judgment, necessitate the termination of their participation in the clinical trial, the case should be withdrawn.(2)If the patient develops other conditions that interfere with trial observations and, in the physician’s judgment, the clinical trial should be terminated, the case will be treated as invalid.(3)If a subject decides during the clinical trial that they no longer wish to participate and requests to withdraw from the study, their request should be respected, and they should be allowed to exit the trial.

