### Safety evaluation and adverse events

Adverse reactions to acupuncture will be evaluated using an adverse reaction assessment form, which includes infections, hematomas, needle syncope, post-needling complications, and other adverse reactions. Throughout the trial, all Serious Adverse Events (SAEs) and Adverse Events (AEs) will be recorded and measured by both the subjects themselves and the acupuncturists. In our trial, SAEs will be defined as events requiring hospitalization, resulting in disability or impaired work capacity, life-threatening conditions, or death. AEs will be classified as treatment-related or non-treatment-related based on their potential correlation with the acupuncture procedure, as determined by the acupuncturist and relevant experts within 24 hours. Given that acupuncture is a minimally invasive treatment, pain that occurs within 30 minutes after needling and resolves spontaneously is not considered an AE due to the inevitable nature of needle-related discomfort. The number of AE cases and treatment sessions will be recorded. We will compare the proportion of subjects who experience treatment-related AEs. Subjects who experience at least one treatment-related adverse reaction will be included in the proportion comparison. If an adverse event is serious and related to this trial, the subject will withdraw from the study and receive appropriate medical care.

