### Statistical analysis

Statistical analysis will be performed using SPSS software version 26.0. Measurement data will be presented as means and standard deviations (SD) or medians and interquartile ranges (IQR), as appropriate. Counting data will be expressed as percentages.

Efficacy evaluation will adhere to the intention-to-treat (ITT) principle, including all patients who have received at least one treatment. For the primary outcome (1-hour pad test) and secondary outcomes (72-hour bladder diary, ICIQ-SF scores, I-QOL scores, pelvic floor muscle strength test results, and patient self-evaluation of efficacy), a mixed-effects model will be employed to account for the characteristics of repeated measures data. The model will include group, time points, and their interaction as fixed effects, with participants treated as random effects. Baseline values will be incorporated as covariates.

Missing data will be handled using multiple imputation. Five datasets will be generated based on age, sex, body mass index (BMI), baseline characteristics, and outcome values at other time points for analysis. Two sensitivity analyses will be performed for the primary outcome (1-hour pad test): (1) an analysis of the dataset without imputation to assess potential bias introduced by imputation and (2) an analysis of the per-protocol (PP) set to evaluate the impact of adherence. The PP set is defined as participants who completed at least 80% of the planned treatments without significant protocol violations (i.e., at least five treatments in both the acupuncture and sham acupuncture groups).

Safety analysis will include all participants who received at least one treatment. AE rates will be described using counts and percentages. Between-group comparisons will be conducted using the chi-square test when the expected frequency requirements are met; otherwise, Fisher’s exact test will be used. All statistical analyses will be two-tailed, with a significance level of *P *< 0.05 considered statistically significant.

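### The protocol does not separate stopping needling from leaving the study, so obtainable week-2 and week-6 pad tests may be lost and imputed in an analysis called ITT

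*Protocol article*

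**What the plan says.** - **Shedding criteria.** Randomised women who "are unable to complete the treatment regimen and observation period specified in the study protocol are considered shedding cases". Treatment and observation are joined in one definition.
- **Management of shedding cases.** After shedding, "efforts should be made to contact them via home visits, scheduled follow-ups, telephone calls, or letters to determine the reasons for shedding". Information is then recorded, "including the date of the last acupuncture session and the evaluation items completed up to that point". All data on these women are kept "both for archival purposes and for inclusion in intention-to-treat (ITT) statistical analysis".
- **Termination criteria.** This covers severe adverse reactions that, "in the physician’s judgment, necessitate the termination of their participation in the clinical trial, the case should be withdrawn". The second item labels as invalid the case of a woman with an interfering condition. The third lets a woman leave on request. None mentions assessment without needling.
- **Safety evaluation and adverse events.** After an event that is both serious and trial-related, "the subject will withdraw from the study and receive appropriate medical care".
- **Statistical analysis.** Efficacy follows ITT in everyone with at least one treatment. "Missing data will be handled using multiple imputation", with five datasets. The pad test also has an unimputed analysis and a per-protocol analysis (at least five sessions).

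**The concern.** An ITT comparison needs each woman's outcome whether or not she finished the needling. The sections on exit give staff no instruction to obtain it once needling stops. Staff who follow them as written would ask why she stopped, file what she had already completed, and leave the rest to imputation.

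The imputation predictors that the protocol names are age, sex, BMI, baseline characteristics and outcomes at other times. Sessions received and the reason for stopping are not among them. A woman who stops before week 2 has no later pad test to inform her imputed value, so that value is modelled largely on women who continued. The two sensitivity analyses do not test this. The unimputed analysis has no outcomes after stopping to use, and the per-protocol set leaves out women with fewer than five sessions.

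Reasons for stopping could well differ by arm, because needling is deep with deqi in one arm and under 2 mm in the other. The between-group difference, SD and effect size that the pilot is meant to supply would carry any resulting distortion. Feasibility is the primary objective, with separate limits for dropout, compliance and data completeness. A merged status lets poor compliance also count as dropout and as missing data.

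**Working it through.** **Inputs from the protocol.** The Sample size section gives 30 per group, a 20% dropout allowance, and 36 per group (72 in total). The Introduction gives the feasibility limits: dropout at most 20%, data completeness at least 90%. The Abstract names two post-baseline times for the primary pad test, week 2 and week 6.

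**1. The plan's own figure.** 30 × 1.20 = 36 per group, and 2 × 36 = 72. It reproduces. No cause of dropout is attached to the 20%.

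**2. Most women who can shed within the limit.** 0.20 × 72 = 14.4, so 14 women.

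**3. Upper bound on lost tests.** Scheduled post-baseline tests: 72 × 2 = 144. If all 14 stop before week 2 and none is assessed again, 14 × 2 = 28 are missing: 28/144 = 19.4%. Then 116/144 = 80.6% are observed. With baseline counted, (216 − 28)/216 = 87.0%. Both lie under the 90% completeness limit, if that limit is counted on pad tests (an assumption, since the protocol does not define it).

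**4. Milder timing.** If all 14 leave after the week-2 test, 14/144 = 9.7% are missing and 90.3% are observed.

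**5. What continued assessment could recover.** Let q be the share of the 14 who would still attend both tests. It is an assumption, and the protocol gives no basis for choosing a value.

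| q | Women without post-baseline tests, 14 × (1 − q) | Share of 72 |
|---|---|---|
| 0 | 14 | 19.4% |
| 0.25 | 10.5 | 14.6% |
| 0.50 | 7 | 9.7% |
| 0.75 | 3.5 | 4.9% |
| 1 | 0 | 0% |

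**6. Possible bias.** Suppose a fraction m of one arm is unobserved and truly differs by δ SD from what is imputed, with no such discrepancy in the other arm (assumptions). The difference between arms is then off by m × δ.
- m = 0.20: 0.20 × 0.25 = 0.05 SD to 0.20 × 1.0 = 0.20 SD.
- m = 0.10: 0.10 × 0.25 = 0.025 SD to 0.10 × 1.0 = 0.10 SD.

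**The case against.** The strongest reply is that the text leaves a point open and does not fix a harmful rule. Much of this stands.

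- A reader might infer that later pad tests are lost by rule. The recording list opens with the word including, so it is not exhaustive. No section forbids assessment after needling stops, and scheduled follow-ups are among the contact routes.
- The shedding definition can be read jointly, so that a woman who stops needling but attends assessments is not shed. The per-protocol threshold likewise implies that women with few sessions stay in the ITT set.
- A reader might take the 20% as the number of women who stop needling. It is an all-cause planning allowance and limit. The two withdrawal clauses for reactions are narrow and could not account for 14 women.
- A reader might conclude that the ITT result rests on imputation. Within the dropout limit, at least about 80% of post-baseline tests are observed, and an unimputed analysis is planned.
- A reader might infer that safety observation stops after a serious related event. The safety section does not say so. It records adverse events throughout the trial and provides medical care.
- This is an article, and a fuller protocol may say more.

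What does not stand is that the matter is therefore only an omission. The article sets out its exit rules in three headed sections and again under safety. Those rules join the two states and direct contact at reasons alone. Being counted in the ITT set does not by itself obtain a woman's outcome. That the text can be read two ways is itself a reason to settle it.

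**Conclusion.** The concern holds in limited form. The protocol does not distinguish stopping study needling from leaving the study, and it nowhere provides for the week-2 or week-6 pad test once needling has stopped. Obtainable primary-outcome data may be lost and imputed in an analysis described as ITT.

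The ceiling within the protocol's own dropout limit is 14 of 72 women, or 28 of 144 post-baseline tests (19.4%). It assumes that all 14 stop before week 2 and that none is reassessed. The real number is unknown and may be much smaller, since the recoverable share depends on how many would agree to attend. The bias range of 0.025 to 0.20 SD illustrates declared assumptions and does not predict this trial. A bias in grams, or a percentage overstatement of the effect, would need stopping rates and outcome differences that the protocol does not give.

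**What to change.** 1. In the shedding, termination and safety sections, define two statuses: stopped study needling, and withdrew consent to follow-up. Leave the rules on who stops treatment as they are.
2. State that women in the first status are invited to the remaining scheduled assessments, including the week-2 and week-6 pad tests, and that adverse-event follow-up continues.
3. Reword the recording instruction so that it covers evaluations up to and after the exit date, unless consent to follow-up is withdrawn.
4. In the Statistical analysis section, say that these observed values enter the ITT analysis and that imputation is kept for data still missing.

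The cost is protocol wording and a CRF entry for the status. The visits are already scheduled. A few women no longer being needled would make extra visits, and some will decline. The article reports recruitment under way since September 2024, so women who had already shed would have been handled under the existing wording, and the report should say so.

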#### Termination criteria.

(1)At least one urologist or gynecologist must participate in this study. If a patient experiences severe adverse reactions that, in the physician’s judgment, necessitate the termination of their participation in the clinical trial, the case should be withdrawn.(2)If the patient develops other conditions that interfere with trial observations and, in the physician’s judgment, the clinical trial should be terminated, the case will be treated as invalid.(3)If a subject decides during the clinical trial that they no longer wish to participate and requests to withdraw from the study, their request should be respected, and they should be allowed to exit the trial.

### Allocation

This study will adopt a single-center randomized controlled trial design, randomly allocating 72 eligible patients into the acupuncture group or sham acupuncture group in a 1:1 ratio (36 patients in each group). A completely random digital sequence will be generated by third-party personnel using computer software, without setting any blocking or stratification factors, to ensure a fully randomized allocation process. After obtaining the patient’s informed consent form (**S2 File**), sequentially numbered, opaque, sealed, tamper-resistant, and water-resistant envelopes made of polypropylene (PP) will be utilized. The exterior of the envelopes will be labeled with only the random number and unsealing instructions, while group assignments will be concealed inside the envelopes to ensure allocation concealment. Recruitment personnel will screen and enroll patients who meet the inclusion criteria and distribute the envelopes in order. Before the intervention, the acupuncturist will open the envelope on-site to determine group assignment and administer the corresponding treatment.

### Blinding

In this trial, blinding will be implemented for participants, outcome assessors, and statistical analysts, with group assignments represented only as A or B. Statistical analysts will conduct the analysis without knowing the actual group assignments, and unblinding will occur only after the statistical analysis is completed. Due to the inherent characteristics of acupuncture, blinding will not be applied to acupuncture practitioners. The roles of acupuncture practitioners, outcome assessors, and statisticians will be carried out by separate individuals to ensure independence and minimize bias. To help maintain participant blinding, adhesive pads will be used in both groups to control for potential biases as much as possible. Unblinding will be permitted only in emergency situations. To assess the success of the blinding process, all participants will be asked to guess whether they received real or sham acupuncture within 5 minutes after their first treatment and again after their final treatment session.

### Interventions

In this trial, all patients will be advised to perform pelvic floor muscle training, following the exercise recommendations of K Bø and KEGEL [15,16]. During the baseline period, all patients will receive instructional guidance from professional rehabilitation physicians at the hospital. Subsequently, patients will be advised to perform pelvic floor muscle training daily, three times per day - morning, noon, and evening. The training program can be found in **S3 File**.

The acupuncture intervention will be conducted by two acupuncturists from the Beijing University of Chinese Medicine Third Affiliated Hospital, each with over 2 years of clinical experience. Patients will receive individual treatment to prevent communication about their treatments. During the treatment period, if a subject is in their menstrual cycle, treatment will be postponed until the end of the cycle. The delay time will not be included in the treatment period. During the trial, patients will not be allowed to use any specialized medications or rehabilitation treatments other than those specified in this research protocol, and any additional details will be reported in the Case Report Form (CRF). Within two weeks, patients will receive acupuncture and sham acupuncture treatments in a supine position, three times per week on alternate days. The specific procedures are as follows.

#### Acupuncture group.

The acupoints selected are bilateral Taichong (LR3), bilateral Sanyinjiao (SP6), and Zhongji (CV3), with the locations following the World Health Organization’s standard acupuncture positions. Patients will be placed in a supine position, and the acupoints will be sterilized with 75% alcohol. Disposable acupuncture needles will be used (diameter 0.30 mm, length 75 mm, Hwato brand, Suzhou Medical Appliance Factory, Ltd., China). Before needling, sterile adhesive pads will be placed on the acupoints. The acupuncture needles will penetrate through the sterile adhesive pads into the acupoints. The needles will be manipulated using lifting, thrusting, and rotational techniques to achieve ‘deqi’ sensation, and retained for 15 minutes. **Table 1** shows the acupoint locations, corresponding needle types, insertion angles, and insertion depths. Meanwhile, the specific acupoint locations are shown in **Fig 3**.

**Table 1 pone.0324384.t001:** Acupoints’ locations, corresponding needle type, Insert angle and depth of insertion.

Acupuncture name	Location	Needle type	Insert angle	Depth of insertion
Tai-chong (LR3)	On the dorsum of the foot, between the first and second metatarsal bones, in the depression distal to the junction of the bases of the two bones, over the dorsalis pedis artery.	0.30 × 75 mm	90°	10 ~ 20mm
San-yin-jiao (SP6)	On the tibial aspect of the leg, posterior to the medial border of the tibia, 3 cun superior to the prominence of the medial malleolus.	0.30 × 75 mm	90°	20 ~ 30mm
Zhong-ji (CV3)	On the lower abdomen, 4 cun inferior to the centre of the umbilicus, on the anterior median line.	0.30 × 75 mm	45°	30 ~ 40mm

1 cun (≈20 mm) is defined as the width of the patient’s thumb interphalangeal joint.

**Fig 3 pone.0324384.g003:**
[figure not shown]
Acupoints. The original image is from the “Dajia Traditional Chinese Medicine App”.

#### Sham acupuncture group.

The selected points are bilateral non-acupoint 1, non-acupoint 2, and unilateral non-acupoint 3. Patients will be placed in a supine position, and the non-acupoint locations will be sterilized with 75% alcohol. Disposable acupuncture needles will be used (diameter 0.30 mm, length 75 mm, Hwato brand, Suzhou Medical Appliance Factory, Ltd., China). Before needling, sterile adhesive pads will be placed on the non-acupoints. The acupuncture needles will penetrate through the sterile adhesive pads into the skin superficially, with insertion depth controlled within 2 millimeters, avoiding the ‘deqi’ sensation, and retained for 15 minutes. **Table 2** shows the non-acupoint locations, corresponding needle types, insertion angles, and insertion depths.

**Table 2 pone.0324384.t002:** Sham acupoints’ locations, corresponding needle type, Insert angle and depth of insertion.

Sham acupuncture name	Location	Needle type	Insert angle	Depth of insertion
Sham acupuncture 1 (SA1)	Between Taichong (LR3) and Gongsun (SP4), between the Liver Meridian and the Spleen Meridian	0.30 × 75 mm	90°	<2 mm
Sham acupuncture 2 (SA2)	1 cun lateral to Sanyinjiao (SP6)	0.30 × 75 mm	90°	<2 mm
Sham acupuncture 3 (SA3)	4 cun above the umbilicus, 1 cun to the left of the anterior midline, between the Kidney Meridian and the Stomach Meridian	0.30 × 75 mm	90°	<2 mm

1 cun (≈20 mm) is defined as the width of the patient’s thumb interphalangeal joint.

### Outcomes

#### Primary outcomes.

The primary outcome in this study is the change in the 1-hour pad test, which is a medical test recommended by the International Continence Society (ICS). The measurement method primarily involves instructing patients to complete a series of movements, and measuring the change in pad weight to determine the amount of urine leakage during the test process. The entire testing process is supervised by researchers, while the placement and removal of the pad is performed by the patients themselves. The 1-hour pad test can objectively and accurately measure the patient’s urine leakage volume and effectively observe changes in leakage volume after treatment, making it an objective and accurate indicator for observing therapeutic efficacy.

#### Secondary outcomes.

**72-hour bladder diary:** This refers to continuously recording (generally for 72 hours) without changing lifestyle or urination habits, documenting the type and volume of fluid intake, times of voluntary urination and volume per urination, as well as observing the severity of urinary incontinence, frequency of incontinence episodes, and pad usage over 72 hours. This can objectively reflect the patient’s urination and urinary incontinence conditions and serves as a means of treatment evaluation. The severity of PSUI will be graded based on urine leakage under normal conditions without strenuous activity (such as vigorous coughing, intense exercise, or heavy lifting) during the past 72 hours: none; mild, a few drops of leakage; moderate, soaking of underwear; severe, leakage soaking through outer clothing. For participants wearing pads, the severity of SUI will be graded as follows. Mild: a few drops of leakage; moderate: multiple leakages with patchy soaking of the pad; severe: single leakage with patchy soaking of the pad.

**ICIQ-SF questionnaire:** The International Consultation on Incontinence Questionnaire-Short Form. Used to investigate the degree of impact of urinary incontinence on patients, the brief questionnaire includes three scored items - frequency of urinary incontinence, amount of leakage, and impact on daily life - as well as a fourth non-scored item assessing the type of urinary incontinence. When filling out the form, patients are instructed to recall their symptoms. The total score of the three scored items constitutes the scale assessment result, with higher values indicating greater severity and lower values indicating less impact of urinary incontinence on the patient’s quality of life. This can relatively objectively quantify the impact on patients’ quality of life and psychological well-being, as well as the changes brought about by treatment.

**I-QOL questionnaire:** Incontinence Quality of Life questionnaire. Used to assess patients’ quality of life, including evaluation of three aspects: psychological impact, social barriers, and behavioral limitations caused by urinary incontinence. It consists of 22 questions, with each question having 5 levels, and each level scoring differently, ranging from 1 to 5 points. A lower total score indicates poorer quality of life due to urinary incontinence. This can relatively objectively quantify the impact on patients’ quality of life and psychological well-being, as well as the changes brought about by treatment.

**Pelvic floor muscle strength assessment:** A comprehensive evaluation is conducted using both instrument-based and manual methods. Instrument-based assessment is performed with the biofeedback rehabilitation device XCH-C1 (Shanghai Nuocheng Electric Co., Ltd.) to measure the strength of Type I and Type II muscle fibers in the pelvic floor before and after treatment. The results are graded on a scale of 0 to V, where 0 indicates no contraction and V indicates strong contraction.

Manual assessment follows the internationally standardized perineal muscle strength testing method, scoring pelvic floor muscle strength on a scale of 0–5 points. Higher scores correspond to stronger muscle strength. The manual grading system is as follows:

0: No contraction is felt.1: Slight contraction is detected by the examiner’s fingers.2: Muscle contraction is present, lasting for 2 seconds and repeated twice.3: Contraction allows the examiner’s fingers to move upward and forward, lasting for 3 seconds and repeated three times.4: Strong contraction resists finger pressure, lasting for 4 seconds and repeated four times.5: Very strong contraction resists finger pressure, lasting for 5 seconds and repeated five times.

**Patient self-assessment of therapeutic efficacy:** Patients will conduct self-evaluations of treatment effectiveness at weeks 2, 4, and 6. A 4-point scale will be used to measure the level of help perceived by participants (0: no help; 1: little help; 2: moderate help; 3: significant help).

**Patient blinding assessment:** All patients will be asked to guess whether they received real or sham acupuncture within 5 minutes after their first treatment and after their final treatment.

**Assessment of other treatment methods:** Throughout the trial period, subjects will not be encouraged to undergo any specific PSUI treatments. For any treatments that have been used, relevant information should be recorded in the case report form. Other treatment methods for PSUI mainly include biofeedback electrical stimulation, vaginal dumbbells, and drug therapy.

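### The bladder-diary severity grade follows two non-equivalent rules chosen by pad use, so if it is analysed over time a change in pad use can move the grade without any change in leakage

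*Protocol article*

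**What the plan says.** The protocol article, under Secondary outcomes (72-hour bladder diary), gives one severity grade with two sets of definitions.

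- The general scale has four levels, ordered by how far the urine gets: "none; mild, a few drops of leakage; moderate, soaking of underwear; severe, leakage soaking through outer clothing".
- A second scale is then introduced: "For participants wearing pads, the severity of SUI will be graded as follows". Its lowest level is mild, worded as on the general scale. Above that it reads "moderate: multiple leakages with patchy soaking of the pad; severe: single leakage with patchy soaking of the pad". No level for absence of leakage is listed.

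The same diary also records "frequency of incontinence episodes, and pad usage over 72 hours". Under Statistical analysis, the 72-hour bladder diary is among the secondary outcomes for which "a mixed-effects model will be employed to account for the characteristics of repeated measures data", with group, time and their interaction as fixed effects and the baseline value as a covariate. The article gives no mapping between the two scales and does not say whether the scale is set once at baseline or chosen afresh at each assessment.

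**The concern.** A grade compared across visits and arms should mean the same thing each time it is recorded. Here the criterion itself changes with pad use: extent of spread on one scale, number of leaks on the other. Pad use is not a fixed characteristic. It is a diary item and may change after randomisation, possibly because a woman is leaking less or feels more confident.

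If the grade is analysed as one repeated measure, part of any change from baseline could come from switching scale. Switching that is similar in both arms adds noise. Switching that differs by arm enters the between-group difference as bias. Separately, two upper grades that overlap leave the assessor to choose between them even for a woman who wears pads throughout.

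**Working it through.** The article states no figure on this point and no formula applies. The check is to apply both definitions to the same pattern of leakage. The inputs are the two scales and the pad-wearing rule, all under Secondary outcomes.

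| Leakage over 72 hours | Graded without a pad | Graded with a pad |
|---|---|---|
| 1. Drops only | mild | mild |
| 2. Several small leaks that together wet the underwear, or a patch of pad, without reaching outer clothing | moderate | moderate |
| 3. One leak that does the same | moderate | severe |
| 4. Several leaks, each enough on its own to wet a patch, none reaching outer clothing | moderate | fits moderate and severe |
| 5. No leakage | none | no listed grade |

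Of these five patterns, two agree (rows 1 and 2), one can disagree by a full grade (row 3), one has two grades on the pad scale (row 4) and one has none (row 5).

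**Switching.** A woman in row 3 who stops wearing pads goes from severe to moderate with the same leak; if she starts, she goes from moderate to severe. A woman in row 5 gains or loses a defined grade in the same way.

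**Overlap.** The pad scale uses the same degree of wetting for both upper grades and separates them only by whether one leak or several produced it. The likely intent is that one leak large enough to make a patch is worse than several small ones that add up to a patch. The text does not say so, and row 4 is left unresolved.

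**Route to the analysis.** The model described under Statistical analysis has no pad-use term. The grade is one of several diary items, and the section names the diary without saying which item is modelled. The effect on the comparison is therefore conditional on the grade being modelled. The defects in the definition are not.

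**The case against.** Several points on the other side are sound.

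- **Row 3 is possible, not demonstrated.** Neither scale gives volumes, and the no-pad scale speaks of soaked underwear while the pad scale speaks of patches. A single leak big enough to mark a pad in that way might also have gone through outer clothing, making it severe on both. The wording permits the disagreement but does not force it.
- **Some pad-specific wording is reasonable.** A pad can stop urine before it reaches clothing, so the general scale cannot simply be carried over. That explains why a second scale exists, but not why its criterion differs without a mapping.
- **The modelled item is not named.** Choosing it is commonly left to an analysis plan that is not shown. This is why the consequence is stated conditionally.
- **The recording instruction might seem to hold pad use constant.** The diary is to be kept "without changing lifestyle or urination habits". This governs behaviour while recording. It does not hold pad use constant from one assessment to the next.

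A reader might also infer that the pad scale scores improvement as worsening, because a woman who goes from several patch-wetting leaks to one would rise from moderate to severe. The documents do not support that as a general statement. It requires grading her moderate first. Read in order of leak size, she was already severe and stays severe. What stands is that the text allows either grade.

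**Conclusion.** The point holds as a defect in how one outcome item is defined. The two rules are not equivalent, the upper pad grades are not mutually exclusive, and a dry pad wearer has no listed grade. If the grade is analysed as a repeated measure, a change in pad use can move it without a change in leakage.

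The size cannot be computed from the document. A reader might be tempted to assume that 30–70% of women wear pads at baseline, that the arms differ by 20 percentage points in stopping, and that each woman who stops shifts one grade, giving 0.3 × 0.2 = 0.06 to 0.7 × 0.2 = 0.14 grade. None of these inputs is in the document. The last is too strong, because rows 1 and 2 do not shift at all, and entry is restricted to mild to moderate incontinence, so row 1 may be common. These figures should not be relied on.

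Nor does the point threaten the trial's main results. The 1-hour pad test, episode frequency, pad count, ICIQ-SF and I-QOL do not use this grade. It is one item of one secondary outcome in a pilot whose stated primary objective is feasibility. It is worth correcting because the correction is cheap and a formal trial could inherit the scale.

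**What to change.** For this pilot:

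- Name incontinence episodes per 72 hours as the diary outcome that enters the mixed-effects model. The diary already records them.
- Report the severity grade descriptively only, split by pad use at that assessment, with no modelling across pad states.

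Before the formal trial reuses the scale:

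- Make the upper pad grades mutually exclusive: several leaks that only together make a patch, versus any single leak that makes one.
- Add a none level for pad wearers.
- Reconcile the two scales, so that a given leak receives the same grade whether or not a pad is worn.

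The scale repair is best kept for the formal trial. Study status reports that recruitment began in September 2024 and was expected to finish by June 2025, so rewording the diary part-way would split the sample between two instruments.

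The change adds no visit, measurement or participant. The downside is that the severity grade loses its inferential comparison in this pilot.
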